**INDEPENDENT CLINICAL RESEARCH PROJECT: PROTOCOL**

|  | File nº |
| --- | --- |
|  | **SPI/2885/2011** |
| **TITLE: Treatment with probiotics (*Saccharomyces boulardii*) and its role in bacterial translocation and immune reconstitution in HIV infection** | |
|  | |
| Principal Investigator: **[name]** | |
| SUMMARY (Objectives and methodology):  **Objectives:** MAIN: To evaluate the parameters of bacterial translocation after treatment with probiotics (*Saccharomyces boulardii*) in HIV+ patients and its role on immune reconstitution. SECONDARY OBJECTIVES: 1) To analize the progress of immune activity markers after the administration of probiotics. 2) To determine the improvement of CD4+ lymphocytes and HIV viral load in patients after taking probiotics.  **Methods:** Design: A prospective randomized open controlled doble-blinded trial, to be performed at a tertiary care hospital in Barcelona. Subjects: Cronic HIV infected patients. Sample size: 44 cases. They´ll be divided in 2 groups: (1) Patients with CD4 +> 400 cells / ml and undetectable viral load for more than two years (22 cases) and (2) Patients with inmunodiscordancy, defined as patients with CD4 + T cells lower than 350 cells / ml despite 4-7 years of effective antiretroviral therapy. (22 cases). Intervention: Patients were randomized in 2 subgroups: (A) they´ll receive daily oral supplementation with *S. boulardii* for 3 months and (B) they ´ll receive placebo. Variables: bacterian lipopolisacarid levels (LBP), parameters of immune activation in plasma (sCD14, IFN-Υ, TNF, IL-2, IL-5, IL-6, IL-12) and fecal microbiome prior to the use of probiotics (baseline), at 3 and 6 months. Immunological and clinical data. Outcome measures: quantification of bacterial translocation levels, markers of activity and 16S rDNA gene amplification and parallel sequencing of fecal microbiome. Analysis: Comparison of variables before and after the intervention. The analysis will be performed by biological and immunological effectiveness. | |

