**INDEPENDENT CLINICAL RESEARCH PROJECT: PROTOCOL**

|  | File nº |
| --- | --- |
|  | **SPI/2885/2011** |
| **PI: [name]** | |
| **Hypothesis**      Oral supplementation with probiotic *Saccharomyces boulardii* decreases enteropathy associated with HIV infection, and consequently, minimizes microbial translocation and chronic immune activation. | |
| **Objectives:**  Principal:  To evaluate the changes on bacterial translocation, systemic inflammation and gut microbiome after treatment with probiotic *(Saccharomyces boulardii)* compared with placebo in HIV-positive patients under an effective ART and its role on immune reconstitution.  Secondary objectives:  1) To analyze the changes in immunoactivity markers after administration of probiotics and their relationship with bacterial translocation.  2) To explore if the immunological non-response was associated with higher systemic inflammation and microbial translocation parameters and a different gut microbiome pattern. | |

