| **Methods**: Population and Study Design  A single-center, randomized, double-blind, placebo controlled pilot study will be conducted in nonconsecutive HIV-1–infected patients aged 18 years or older.  Patients will be recruited at a tertiary care hospital (Institut Hospital del Mar d'Investigacions Mediques) in Barcelona, Spain.  All patients have chronic HIV infection, undetectable plasma viral load (,20 copies per milliliter) for at least 2 years, and a stable HAART regimen. It will be divided into 2 groups:  - Group 1 (n=22): Patients with CD4 +> 400 cells / ml and undetectable viral load for more than two years.  - Group 2(n=22): Discordant patients, deﬁned by an unfavorable persistent immunologic response (T-CD4+ cells <350 cells per microliter) despite long-term suppressed viral load (4-7 years).    Randomization:  A computer-generated randomization list will be used. Randomization will be performed by a hospital pharmacist unrelated to the care of the patients, using sequentially numbered containers. The participants and the care providers will be blinded after assignment to interventions.  Patients in both groups (1 and 2) will be randomized in 2 subgroups:  (A) 22 will receive daily oral *S. boulardii* supplementation for 3 months.  (B) 22 will receive white placebo patients (lactose) for 3 months.  Exclusion criteria:  - Patients who receive or have received in the last 6 months food supplements containing probiotics.  - Patients who have received antibiotic treatment in the last two months, or HIV patients who usually require to take antibiotics more than 2 times at year.  - Patients with presupposing poor adherence to dietary supplements or HAART.  - Changes in HAART regimen in the previous 2 years, and presence of a serious concomitant disease or substantial abnormalities in the laboratory tests that prevented study participation.  - Patients who do not sign the informed consent.  * Current antibiotic treatment during the study or the presence of any acute concomitant illness will not exclude patients out of the study.  **Intervention:**  - The intervention will be carried out an expert physician in Infectious Diseases.  - Daily treatment to all patients (S. boulardii VS placebo) will be prescribed at baseline in doses of 2 capsules every 12 hours, at least half an hour before intake, during 12 weeks.  - Extraction of blood samples and stool collection will be performed before starting probiotics (baseline) at 3 and 6 months.   In each case the following variables will be included in the data collection:  - Demographic affiliation, height, weight, toxic habits, depositional habit (BRISTOL scale).  - The HANDS scale of anxiety / depression will be apply.  - Dates of start and end of past and current antiretroviral medication will be recorded and concomitant medication administered during the study, including antibiotics.  - Any possible adverse effects of the intervention or serious adverse event will be recorded.  - Adherence to treatment will be registered, counting returned capsules on each visit.  **Study/Clinical Assessment:**  The primary end point of the study will be changes in serum LBP levels as a marker of microbial translocation.  Secondary endpoints will be as follows:   - Changes in markers of immune activity, including serum concentrations of soluble CD14 (sCD14), tumor necrosis factor alpha (TNF-a), interleukin 6 (IL-6), high-sensitivity C-reactive protein (Hs-CRP), B2 microglobulin, erythrocyte sedimentation rate, IL-2, IL-5, IL-12, D-dimer, IFN-Υ, ﬁbrinogen, Ig G, and Ig E. - Changes in immune status (T-CD4+ and T-CD8+ lymphocyte count) and HIV-viral load. - Analysis of gut microbioma by 16s rRNA sequencing. - Safety and tolerability.   **After screening for eligibility**, subjects will be visited at baseline (start of treatment), at week 12 (treatment discontinuation), and at week 24 (3 months after discontinuation of treatment).  Clinical and demographic data of the study patients will be collected from the medical records.  **At baseline**, eligible patients were randomized (1:1) to receive treatment with S. boulardii (2 capsules 3 times a day or 6 · 107 living bacteria) or placebo (2 capsules 3 times a day) for 12 weeks.  - Data collection: The data collected will be included in a database specifically designed for this protocol.  - Procedure:   - At each visit (Baseline, week 12 and week 24), clinical assessment and adverse events will be recorded, and blood samples were collected into 9 mL Vacuette serum separator tubes (Greiner Bio-One GmbH, Kremsmünster, Austria). Within 30 minutes after puncture, blood was centrifuged at 3000 rpm for 15 minutes, and serum samples were aliquoted and stored at 280°C until analysis. For all the tests, thawed serum samples were vortexed and centrifuged at 14,000 rpm for 10 minutes before testing. - All patients also provided 50gr of stool samples at each visit (Baseline, week 12 and week 24) , which will be stored at -80°C within the first 24-48 hours; to compare gut microbiome composition before and after a 12-week treatment with probiotic or placebo. - Once all samples will be collected, they will be sent together on dry ice to the Reference Laboratory of Catalonia, where they will be analyzed.   - Plasma and faecal sample Analysis:   - Inﬂammation Markers For analysis of IL-6 and TNF-a, the Milliplex MAP assay on a ﬂuorescent microsphere-based instrument (Merck Millipore, Merck KGaA, Darmstadt, Germany; Luminex/Bioplex200-Luminex Corp., Austin, TX and BioRad, Hercules, CA) will be used. Multianalyte proﬁling of serum concentrations will be performed using a commercially available multiplex immunoassay kit (HSCYTMAG-60K; Millipore, Billerica, MA). - Hs-CRP and b2 microglobulin will be measured using the Immulite chemiluminescent immunometric assay on its automated analyzer (Immulite One; Siemens Healthcare, Llanberis, United Kingdom). Plasma ﬁbrinogen will be measured using the Clauss coagulative method with HemosIL reactives (Instrumentation Laboratory, Bedford, MA). - Microbial Translocation Markers Serum levels of soluble CD14 will be quantiﬁed in duplicate with a commercially available enzyme-linked immunosorbent assay kit (Quantikine; R&D Systems, Minneapolis, MN) using a Quanta-Lyser 160 robotic workstation (Inova Diagnostics, San Diego, CA). - Serum LBP will be measured using the Immulite chemiluminescent immunometric assay on its automated analyzer. All assays will be performed according to the manufacturer’s instructions. - Fecal Microbiome Analyses:DNA will be extracted from frozen stool samples and amplified by PCR targeting 16S gene regions using primers described elsewhere ([Klindworth A](http://www.ncbi.nlm.nih.gov/pubmed/?term=Klindworth A%5BAuthor%5D&cauthor=true&cauthor_uid=22933715),[Nucleic Acids Res.](http://www.ncbi.nlm.nih.gov/pubmed/22933715) 2013). We will performed library preparation followed by Illumina sequencing according to standard protocols described previously (Caporaso JG, [ISME J.](http://www.ncbi.nlm.nih.gov/pubmed/?term=Caporaso+JG%2C+Lauber+CL%2C+Walters+WA%2C+Berg-Lyons+D%2C+Huntley+J%2C+Fierer+N%2C+Owens+SM%2C+Betley+J%2C+Fraser+L%2C+Bauer+M%2C+Gormley+N%2C+Gilbert+JA%2C+Smith+G%2C+Knight+R.+2012.+Ultra-high-throughput+microbial+community+analysis+on+the+Illumina+HiSeq+and+MiSeq+platforms.+2012.+ISME+J) 2012). The taxonomic composition of the intestinal microbiota will be characterized by grouping sequences into OTUs (Organizational Taxonomic Units).   Statistical analysis and bioinformatics:   - Student t test was used to assess differences between 2 mean values, and a Mann–Whitney U test was performed when data were not normally distributed. Either the x2 test or the Fisher exact test was used to test the degree of association of categorical variables. Statistical signiﬁcance was set at P , 0.05. Statistical analyses were performed using SPSS software version 20.0 (SPSS, Inc, Chicago, IL). - Microbiome Taxonomy Analyses & Bioinformatics: We used the QIIME open source algorithm for handling and interpretation of the data from the raw sequences; following quality assessment of sequence data, we assigned taxonomic affiliations using the RDP_classifier from the Ribosomal Database Project ( Wang, Q, Appl Environ Microbiol. 2007).   Ethics Committee  The study was approved by the Ethics Committee of Hospital del Mar Medical Research Institute, according to the principles expressed in the [Declaration of Helsinki](http://www.wma.net/en/30publications/10policies/b3/index.html) (annexed). Written informed consent will be obtained from all participants before enrollment in the study (annexed).  **Intervention:**  Aspects related to the investigational medicinal product (manufacture, labeling, distribution ...)  Probiotic: Trade name: Ultra - Levura ® lyophilized   - Responsible for manufacturing: BIOCODEX. - Drug marketed and distributed in Spain by Zambon Laboratories S.A. - Presentation: container with 50 capsules. - quantitative composition: Each capsule contains 1,000 million live bacteria (107) *Saccharomyces boulardii 17* lyophilised: 56.5 mg. Excipients: Sucrose (92.3mg), magnesium stearate q.s. - Laboratory Sales Price: 5.51 € / bottle of 50 tablets.   White Placebo: Sucrose   - Responsible for manufacturing: Kern Pharma   **Funding sources:** Helps independent clinical research of the Ministry of Health No. SPI / 2885/2011 |

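### The summary's analysis sentence states only a before-after comparison, at odds with the placebo-controlled objective, and the test list does not say which contrast it serves

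*Protocol*

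**What the plan says.** Four places in the protocol bear on the contrast.

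- **Summary, Analysis.** The contrast is given as "Analysis: Comparison of variables before and after the intervention". No arm is named. The summary's main and secondary objectives likewise speak of what happens after probiotics, without placebo, although its Intervention item does describe randomisation to *S. boulardii* or placebo.
- **Objectives, Principal.** The aim is to evaluate changes "after treatment with probiotic *(Saccharomyces boulardii)* compared with placebo in HIV-positive patients".
- **Methods.** The trial is "A single-center, randomized, double-blind, placebo controlled pilot study". Under Study/Clinical Assessment, "The primary end point of the study will be changes in serum LBP levels as a marker of microbial translocation". That sentence names neither the visit nor the comparison. Under Procedure, stool samples are collected "to compare gut microbiome composition before and after a 12-week treatment with probiotic or placebo".
- **Statistical analysis and bioinformatics.** For continuous data, "Student t test was used to assess differences between 2 mean values, and a Mann–Whitney U test was performed" when normality fails. The section does not say whether the two means belong to two arms, two immune-response groups or two visits. It names neither a signed-rank test nor an explicitly paired t test.

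**The concern.** A change in LBP can be tested within an arm, against zero, or between arms. Only the second uses the randomisation and answers the principal objective. Drift over calendar time, season and regression to the mean can move both arms together. A before-after test attributes that movement to treatment; a comparison of change between arms cancels it.

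The summary points to the first kind of test and the objective to the second. The test list could have settled the matter but does not identify its contrast. An analyst who followed the summary literally could report a significant fall on probiotic beside a non-significant one on placebo and call this an effect, which it is not. The same analyst would find no rank test for paired data in the list: Mann–Whitney assumes independent samples, and baseline and follow-up values of one patient are not independent.

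**Working it through.** The protocol gives no effect size, SD, correlation or power, so it has no figure of its own to reproduce. The check has two parts.

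**1. Which reading fits the text?**

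| Reading | Principal objective | Summary's Analysis sentence | Named tests |
| --- | --- | --- | --- |
| Before versus after, within arm | does not fit | fits | Mann–Whitney invalid; Student t valid only if paired, which is not stated |
| Change from baseline, between arms | fits | does not fit | both valid |

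Neither reading agrees with all three places, so some current wording has to change. The objective and the tests agree with each other on the between-arm reading. The summary sentence is the one out of line.

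**2. What would the before-after reading cost?** This is an illustration only.

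Inputs from the protocol: 22 patients per arm (22 + 22 = 44) and significance level 0.05. Assumptions: two-sided tests, normal data with SD 1 at each visit, within-patient correlation ρ, and a drift δ towards benefit that is the same in both arms, so there is no true treatment effect.

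*(a) Paired test in each arm, effect claimed if significant on probiotic but not on placebo.* The SD of the change is √(2(1−ρ)), and the non-centrality is δ√22 / √(2(1−ρ)). If p is the within-arm chance of significance, the false claim has probability p(1−p).

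At ρ = 0.5 the SD of the change is 1:

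- δ = 0.25: non-centrality 1.17, p = 0.20, p(1−p) = 0.16.
- δ = 0.30: non-centrality 1.41, p = 0.27, p(1−p) = 0.20.
- δ = 0.42: non-centrality 1.97, p = 0.47, p(1−p) = 0.25.
- δ = 0.50: non-centrality 2.35, p = 0.61, p(1−p) = 0.24.

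With no drift, a false benefit needs significance in the favourable direction on probiotic and none on placebo: 0.025 × 0.95 = 0.024.

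At δ = 0.5 the dependence on ρ is strong. The figure is 25%, 24%, 14% to 15% and 0.1% at ρ = 0.3, 0.5, 0.7 and 0.9. The last is small because both arms are then almost always significant. At ρ = 0.9 and δ = 0.25, p = 0.71 and p(1−p) is again 21%.

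*(b) Between-arm t test on change scores.* In 20,000 simulated trials with a common drift of 0.5 SD, the two-sided type I error was 0.047 to 0.050 for ρ from 0.3 to 0.9. Half of the nominal 5%, or 2.5%, is false benefit.

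*(c) Independent-sample test applied to before-after pairs within one arm.* By normal approximation its true size is 2(1 − Φ(1.96/√(1−ρ))), which is 0.6% at ρ = 0.5 and 0.03% at ρ = 0.7, instead of 5%. Simulation with n = 22 gave 0.7% and 0.1%. For a true change of 0.5 SD at ρ = 0.5, simulated power was 33%, against 61% for the paired t test. The error is conservative: it loses power and does not create false positives.

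If the rule in (a) were applied with independent tests at ρ = 0.5, the false-claim rate would be about 6% at δ = 0.25 and 22% at δ = 0.5.

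**The case against.** The strongest reply is that the between-arm comparison was always intended. The objective, the design and 1:1 allocation all keep placebo in view. The summary sentence may describe only the measured quantity, change from baseline. The stool wording gives a reason for sampling and names both arms. A list of independent-sample tests with no paired test suggests two independent groups. On change scores those tests hold their level.

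Much of this stands, and it rules out two stronger readings that a reader might infer.

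- *That the plan discards the randomised control.* It does not. Nothing in the protocol excludes the comparison with placebo.
- *That the plan uses the wrong test on paired data.* No sentence applies the t test or Mann–Whitney to baseline against follow-up. That reading joins the summary to the statistics section in a way the protocol does not, and the t test is not described as unpaired.

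The illustrative rates are also open to challenge. They rest on an assumed drift and on a decision rule that the protocol never states.

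A statistical analysis plan, if there is one, may properly assign tests to variables and visits, so the missing paired test is not in itself a fault. But such a plan would not remove a sentence in the protocol that states a contrast at odds with the principal objective. That conflict survives the reply.

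**Conclusion.** The point holds as a conflict in the protocol's own text. The summary's only analysis contrast is before versus after, the principal objective is against placebo, and the statistics section does not say which of the two its tests serve. The named tests fit a between-arm comparison of change, and Mann–Whitney would be invalid for before-after pairs. The protocol does not show that a wrong analysis will be done.

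The possible damage can only be illustrated. With 22 per arm and paired within-arm tests, a misleading contrast of significance arises in about 16% to 25% of trials at correlation 0.5 and a common drift of 0.25 to 0.5 SD. It arises in about 2.4% with no drift, and in about 0.1% at correlation 0.9 with 0.5 SD drift. A valid between-arm test gives a false benefit in 2.5%. Drift and correlation are assumptions throughout. Because the wording governs the primary inference, it should be settled before the data are analysed.

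**What to change.** Replace the summary's analysis sentence with: *The treatment effect is the between-arm difference (S. boulardii minus placebo) in within-patient change from baseline, with 95% CI.* Name the change in LBP from baseline to week 12 as the primary contrast, and say in the statistics section that the listed tests compare arms on change.

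Adjusting that comparison for baseline LBP and immune-response group, for example by ANCOVA, uses data already planned and is a free gain.

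Apply the same between-arm rule to the microbiome comparison. Present before-after changes within an arm as descriptive; if they are tested, use the paired t or Wilcoxon signed-rank test.

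The cost is a few sentences of wording. No extra patients, visits or measurements are needed.

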**INDEPENDENT CLINICAL RESEARCH PROJECT: PROTOCOL**

|  | File nº |
| --- | --- |
|  | **SPI/2885/2011** |
| **PI: [name]** | |
| **Hypothesis**      Oral supplementation with probiotic *Saccharomyces boulardii* decreases enteropathy associated with HIV infection, and consequently, minimizes microbial translocation and chronic immune activation. | |
| **Objectives:**  Principal:  To evaluate the changes on bacterial translocation, systemic inflammation and gut microbiome after treatment with probiotic *(Saccharomyces boulardii)* compared with placebo in HIV-positive patients under an effective ART and its role on immune reconstitution.  Secondary objectives:  1) To analyze the changes in immunoactivity markers after administration of probiotics and their relationship with bacterial translocation.  2) To explore if the immunological non-response was associated with higher systemic inflammation and microbial translocation parameters and a different gut microbiome pattern. | |

| **Methods**: Population and Study Design  A single-center, randomized, double-blind, placebo controlled pilot study will be conducted in nonconsecutive HIV-1–infected patients aged 18 years or older.  Patients will be recruited at a tertiary care hospital (Institut Hospital del Mar d'Investigacions Mediques) in Barcelona, Spain.  All patients have chronic HIV infection, undetectable plasma viral load (,20 copies per milliliter) for at least 2 years, and a stable HAART regimen. It will be divided into 2 groups:  - Group 1 (n=22): Patients with CD4 +> 400 cells / ml and undetectable viral load for more than two years.  - Group 2(n=22): Discordant patients, deﬁned by an unfavorable persistent immunologic response (T-CD4+ cells <350 cells per microliter) despite long-term suppressed viral load (4-7 years).    Randomization:  A computer-generated randomization list will be used. Randomization will be performed by a hospital pharmacist unrelated to the care of the patients, using sequentially numbered containers. The participants and the care providers will be blinded after assignment to interventions.  Patients in both groups (1 and 2) will be randomized in 2 subgroups:  (A) 22 will receive daily oral *S. boulardii* supplementation for 3 months.  (B) 22 will receive white placebo patients (lactose) for 3 months.  Exclusion criteria:  - Patients who receive or have received in the last 6 months food supplements containing probiotics.  - Patients who have received antibiotic treatment in the last two months, or HIV patients who usually require to take antibiotics more than 2 times at year.  - Patients with presupposing poor adherence to dietary supplements or HAART.  - Changes in HAART regimen in the previous 2 years, and presence of a serious concomitant disease or substantial abnormalities in the laboratory tests that prevented study participation.  - Patients who do not sign the informed consent.  * Current antibiotic treatment during the study or the presence of any acute concomitant illness will not exclude patients out of the study.  **Intervention:**  - The intervention will be carried out an expert physician in Infectious Diseases.  - Daily treatment to all patients (S. boulardii VS placebo) will be prescribed at baseline in doses of 2 capsules every 12 hours, at least half an hour before intake, during 12 weeks.  - Extraction of blood samples and stool collection will be performed before starting probiotics (baseline) at 3 and 6 months.   In each case the following variables will be included in the data collection:  - Demographic affiliation, height, weight, toxic habits, depositional habit (BRISTOL scale).  - The HANDS scale of anxiety / depression will be apply.  - Dates of start and end of past and current antiretroviral medication will be recorded and concomitant medication administered during the study, including antibiotics.  - Any possible adverse effects of the intervention or serious adverse event will be recorded.  - Adherence to treatment will be registered, counting returned capsules on each visit.  **Study/Clinical Assessment:**  The primary end point of the study will be changes in serum LBP levels as a marker of microbial translocation.  Secondary endpoints will be as follows:   - Changes in markers of immune activity, including serum concentrations of soluble CD14 (sCD14), tumor necrosis factor alpha (TNF-a), interleukin 6 (IL-6), high-sensitivity C-reactive protein (Hs-CRP), B2 microglobulin, erythrocyte sedimentation rate, IL-2, IL-5, IL-12, D-dimer, IFN-Υ, ﬁbrinogen, Ig G, and Ig E. - Changes in immune status (T-CD4+ and T-CD8+ lymphocyte count) and HIV-viral load. - Analysis of gut microbioma by 16s rRNA sequencing. - Safety and tolerability.   **After screening for eligibility**, subjects will be visited at baseline (start of treatment), at week 12 (treatment discontinuation), and at week 24 (3 months after discontinuation of treatment).  Clinical and demographic data of the study patients will be collected from the medical records.  **At baseline**, eligible patients were randomized (1:1) to receive treatment with S. boulardii (2 capsules 3 times a day or 6 · 107 living bacteria) or placebo (2 capsules 3 times a day) for 12 weeks.  - Data collection: The data collected will be included in a database specifically designed for this protocol.  - Procedure:   - At each visit (Baseline, week 12 and week 24), clinical assessment and adverse events will be recorded, and blood samples were collected into 9 mL Vacuette serum separator tubes (Greiner Bio-One GmbH, Kremsmünster, Austria). Within 30 minutes after puncture, blood was centrifuged at 3000 rpm for 15 minutes, and serum samples were aliquoted and stored at 280°C until analysis. For all the tests, thawed serum samples were vortexed and centrifuged at 14,000 rpm for 10 minutes before testing. - All patients also provided 50gr of stool samples at each visit (Baseline, week 12 and week 24) , which will be stored at -80°C within the first 24-48 hours; to compare gut microbiome composition before and after a 12-week treatment with probiotic or placebo. - Once all samples will be collected, they will be sent together on dry ice to the Reference Laboratory of Catalonia, where they will be analyzed.   - Plasma and faecal sample Analysis:   - Inﬂammation Markers For analysis of IL-6 and TNF-a, the Milliplex MAP assay on a ﬂuorescent microsphere-based instrument (Merck Millipore, Merck KGaA, Darmstadt, Germany; Luminex/Bioplex200-Luminex Corp., Austin, TX and BioRad, Hercules, CA) will be used. Multianalyte proﬁling of serum concentrations will be performed using a commercially available multiplex immunoassay kit (HSCYTMAG-60K; Millipore, Billerica, MA). - Hs-CRP and b2 microglobulin will be measured using the Immulite chemiluminescent immunometric assay on its automated analyzer (Immulite One; Siemens Healthcare, Llanberis, United Kingdom). Plasma ﬁbrinogen will be measured using the Clauss coagulative method with HemosIL reactives (Instrumentation Laboratory, Bedford, MA). - Microbial Translocation Markers Serum levels of soluble CD14 will be quantiﬁed in duplicate with a commercially available enzyme-linked immunosorbent assay kit (Quantikine; R&D Systems, Minneapolis, MN) using a Quanta-Lyser 160 robotic workstation (Inova Diagnostics, San Diego, CA). - Serum LBP will be measured using the Immulite chemiluminescent immunometric assay on its automated analyzer. All assays will be performed according to the manufacturer’s instructions. - Fecal Microbiome Analyses:DNA will be extracted from frozen stool samples and amplified by PCR targeting 16S gene regions using primers described elsewhere ([Klindworth A](http://www.ncbi.nlm.nih.gov/pubmed/?term=Klindworth A%5BAuthor%5D&cauthor=true&cauthor_uid=22933715),[Nucleic Acids Res.](http://www.ncbi.nlm.nih.gov/pubmed/22933715) 2013). We will performed library preparation followed by Illumina sequencing according to standard protocols described previously (Caporaso JG, [ISME J.](http://www.ncbi.nlm.nih.gov/pubmed/?term=Caporaso+JG%2C+Lauber+CL%2C+Walters+WA%2C+Berg-Lyons+D%2C+Huntley+J%2C+Fierer+N%2C+Owens+SM%2C+Betley+J%2C+Fraser+L%2C+Bauer+M%2C+Gormley+N%2C+Gilbert+JA%2C+Smith+G%2C+Knight+R.+2012.+Ultra-high-throughput+microbial+community+analysis+on+the+Illumina+HiSeq+and+MiSeq+platforms.+2012.+ISME+J) 2012). The taxonomic composition of the intestinal microbiota will be characterized by grouping sequences into OTUs (Organizational Taxonomic Units).   Statistical analysis and bioinformatics:   - Student t test was used to assess differences between 2 mean values, and a Mann–Whitney U test was performed when data were not normally distributed. Either the x2 test or the Fisher exact test was used to test the degree of association of categorical variables. Statistical signiﬁcance was set at P , 0.05. Statistical analyses were performed using SPSS software version 20.0 (SPSS, Inc, Chicago, IL). - Microbiome Taxonomy Analyses & Bioinformatics: We used the QIIME open source algorithm for handling and interpretation of the data from the raw sequences; following quality assessment of sequence data, we assigned taxonomic affiliations using the RDP_classifier from the Ribosomal Database Project ( Wang, Q, Appl Environ Microbiol. 2007).   Ethics Committee  The study was approved by the Ethics Committee of Hospital del Mar Medical Research Institute, according to the principles expressed in the [Declaration of Helsinki](http://www.wma.net/en/30publications/10policies/b3/index.html) (annexed). Written informed consent will be obtained from all participants before enrollment in the study (annexed).  **Intervention:**  Aspects related to the investigational medicinal product (manufacture, labeling, distribution ...)  Probiotic: Trade name: Ultra - Levura ® lyophilized   - Responsible for manufacturing: BIOCODEX. - Drug marketed and distributed in Spain by Zambon Laboratories S.A. - Presentation: container with 50 capsules. - quantitative composition: Each capsule contains 1,000 million live bacteria (107) *Saccharomyces boulardii 17* lyophilised: 56.5 mg. Excipients: Sucrose (92.3mg), magnesium stearate q.s. - Laboratory Sales Price: 5.51 € / bottle of 50 tablets.   White Placebo: Sucrose   - Responsible for manufacturing: Kern Pharma   **Funding sources:** Helps independent clinical research of the Ministry of Health No. SPI / 2885/2011 |
| --- |
|  |

| **INDEPENDENT CLINICAL RESEARCH PROJECT: PROTOCOL** | File nº |
| --- | --- |
|  | **SPI/2885/2011** |
| **PI: [name]** | |
| **Workplan**  The project will take place at the Hospital del Mar, following different stages:  PHASE 1: (Duration: 3 months)  - Selection of patients included in the study.  - Check circuit extraction and processing of samples.  PHASE 2: (6 months)  - Recruitment, inclusion and randomization of patients.  - Administration of probiotics in a controlled manner Basal visit at 3 months and 6 months in the randomly selected group.  - Obtain baseline data and plasma samples and feces, at 3 and 6 months of patients.  - Storing data in the database designed for this purpose.  - Preliminary analysis of the data.  PHASE 3: (12 months)  - Monitoring patients in the last month.  - Final data analysis.  - Publication of the results and communicate them in an international congress. | |

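### The protocol randomises within two CD4-defined strata, but its stated between-arm tests ignore them and no by-stratum effect on CD4 change is given

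*Protocol*

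**What the plan says.** The principal objective (Protocol, Objectives) covers translocation, inflammation and microbiome under probiotic against placebo, and "its role on immune reconstitution". It refers to HIV-positive patients on effective therapy in general, not to one CD4 group.

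The sample is built from two groups (Protocol, Methods, Population and Study Design): "Group 1 (n=22): Patients with CD4 +> 400 cells / ml and undetectable viral load for more than two years", and "Group 2(n=22): Discordant patients", the latter with CD4 below 350 despite 4 to 7 years of viral suppression. Under Randomization, "Patients in both groups (1 and 2) will be randomized in 2 subgroups", with 22 patients per arm overall.

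Under Study/Clinical Assessment, change in serum LBP is the primary endpoint. CD4 change is among the secondary endpoints: "Changes in immune status (T-CD4+ and T-CD8+ lymphocyte count) and HIV-viral load". It is not tied to either group.

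The section Statistical analysis and bioinformatics says for continuous data: "Student t test was used to assess differences between 2 mean values", with Mann-Whitney if the data are not normal. Neither test includes the CD4 group. The one objective that uses the groups, the second secondary objective, compares non-responders with the others on inflammation, translocation and microbiome. That compares the groups with each other; it is not a treatment effect within them.

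**The concern.** The design creates a stratum on CD4 status and the stated analysis does not use it. Two consequences follow.

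First, an unstratified comparison leaves any difference in mean CD4 change between the strata in the error term. It also gives no protection if the arms are not balanced within strata, and the protocol does not state such balance.

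Second, persistent poor CD4 recovery is what defines Group 2, so a treatment effect on CD4 could plausibly differ between the strata. If it is concentrated in Group 2 and the arms are compared across all 44 patients, the overall difference is smaller than the Group 2 effect. A null result could then be read as no effect on immune reconstitution. A main-effect term for stratum removes the first problem but not the second; only estimates by stratum show it.

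**Working it through.** **The plan's own figures.** 22 + 22 = 44 holds by CD4 group and by arm. The protocol gives no effect size, SD or power, so no power statement can be reproduced.

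**Inputs from the protocol.** 22 patients per CD4 group; 22 per arm, 1:1; significance level 0.05.

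**Assumptions.** Two-sided test; even split within strata, so 22/2 = 11 per arm per stratum; equal SD of CD4 change in both strata; no difference in mean placebo-arm change between strata. Let d be the Group 2 effect in SD units and f the Group 1 effect as a fraction of d. The protocol gives neither, so a range is shown.

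**Effect seen.** With strata of equal size the pooled effect is d(1 + f)/2. At f = 0 it is d/2.

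**Noncentrality of the two-sample t test** (effect × √(n/2), n per arm):
- Pooled, n = 22: [d(1 + f)/2] × √11. At d = 1.0, f = 0: 0.5 × 3.317 = 1.66.
- Group 2 only, n = 11: d × √5.5. At d = 1.0: 2.35.
- Ratio at f = 0: 2.35/1.66 = 1.41. Group 2 alone gives the stronger signal despite half the patients.

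**Break-even.** Setting the two equal gives (1 + f)/2 = √5.5/√11 = 0.707, so f = 0.41. Above this the pooled test is stronger.

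**Power** (noncentral t, two-sided 0.05):

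| Group 2 effect d | Pooled, f = 0 | Pooled, f = 0.25 | Pooled, f = 0.5 | Pooled, f = 1 | Group 2 only |
| --- | --- | --- | --- | --- | --- |
| 0.8 SD | 25% | 37% | 49% | 74% | 43% |
| 1.0 SD | 37% | 53% | 68% | 90% | 61% |
| 1.2 SD | 49% | 68% | 83% | 97% | 76% |
| 1.5 SD | 68% | 86% | 95% | over 99% | 92% |

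**Unequal SD.** If CD4 change in Group 1 has 1.5 to 2 times the SD of Group 2, pooled power at d = 1.2, f = 0 falls from 51% to between 35% and 24% (normal approximation).

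**What by-stratum results can deliver.**
- 95% CI half-width at 11 per arm: 2.086 × √(2/11) = 2.086 × 0.426 = 0.89 SD.
- The interaction contrast has standard error √(4/11) = 0.603 SD. At f = 0 its power (normal approximation) is 38% for d = 1.0 (1.0/0.603 = 1.66, against 1.96) and 51% for d = 1.2.
- Two separate stratum tests at 0.05 carry a joint false-positive risk of 1 − 0.95² = 9.75%.

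**The case against.** The strongest reply is that the point rests on an absence. The protocol never says the two groups are pooled for CD4, and a sentence about comparing two means fits a comparison within Group 2 as well as one across all patients. Interaction terms for a secondary endpoint are often left to the statistical analysis plan, which is not shown and may contain them. The primary endpoint is LBP, and the trial calls itself a pilot.

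Much of this stands. Pooling is an inference, and the loss of power must be stated as conditional on it. What remains is that the protocol does fix its between-arm tests, and those tests do not use the strata it randomises within. That is a mismatch between the stated design and the stated analysis, beyond detail left for later.

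A reader might also infer that Group 1 has already reconstituted, so that only Group 2 can answer the reconstitution question and pooling necessarily dilutes the effect. The documents do not support this. Group 1 is defined by CD4 above 400 with no upper limit, and nothing says recovery is complete or that counts cannot rise. The objectives cover all patients; the Summary's objective on CD4 improvement is not restricted to a group either. With f above 0.41, pooling is the better choice.

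**Conclusion.** The point holds as a mismatch between design and analysis that should be corrected at low cost; it does not show that the CD4 comparison will fail. The stated between-arm tests for continuous endpoints ignore the CD4 stratum, and no treatment effect by stratum is stated for CD4 change.

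The size depends on the unknown Group 1 effect. At d = 1.0, the pooled test ranges from 24 percentage points worse than Group 2 alone (37% against 61%, no Group 1 effect) to 29 points better (90% against 61%, equal effects). This rests on a pooled analysis, an even split within strata and equal SDs, none of which the protocol states. Because the documents do not settle which case applies, the overall and by-stratum estimates should both be shown.

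**What to change.** In Statistical analysis and bioinformatics, state that CD4 change will be analysed with a linear model containing arm and CD4 stratum, and that the arm effect from this model is the overall estimate. Pre-specify a second model adding the arm-by-stratum term, and report the arm effect with 95% CI in Group 1 and in Group 2. Label the by-stratum results exploratory, and do not name the Group 2 result as the sole answer to the objective. State whether allocation is balanced within each stratum.

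The cost is a few lines of text and analysis on data already collected: no extra patients, visits or assays. The downsides are wide by-stratum intervals and an interaction test of low power, so a non-significant interaction must not be read as evidence that the effect is the same in both groups.
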